### 203 **4.2 Secondary Efficacy Outcomes**

- 204 1. Proportion of recurrent stroke (ischemic stroke and intracerebral hemorrhage) at 3 months and 12 months
- 205 after randomization;
- 206 2. Proportion of patients with functional independence ( $mRS \leq 2$ ) at 12 months after randomization;
- 207 3. Proportion of patients with no or minimal disability ( $mRS \leq 1$ ) at 3 months and 12 months after
- 208 randomization;
- 209 4. Change in NIHSS score at 3 months after randomization;
- 210 5. Proportion of composite cerebrovascular events (ischemic stroke, intracerebral hemorrhage, myocardial
- 211 infarction, and vascular death) at 3 months and 12 months after randomization;
- 212 6. Difference of EuroQoL Group 5-Dimension (EQ-5D) score at 3 months and 12 months after
- 213 randomization;
- 214 7. Change in Barthel Index (BI) score at 3 months and 12 months after randomization;
- 215 8. Difference of platelet counts and coagulation indicators (prothrombin time, and activated partial
- 216 thromboplastin time) at 3 months after randomization.

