#### **13.1 Analysis Cohorts**

##### **13.1.1 Modified Intention-To-Treat Cohort**

According to the basic principle of intention-to-treat analysis, all patients after randomization who received at least one record for drug administration and efficacy evaluation will be included in the modified intention-to-treat cohort. During analysis with the modified intention-to-treat cohort, missing values will be estimated using the last observation carried forward method. The modified intention-to-treat population will be the primary population for efficacy evaluation in this study.

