##### **13.2.2 Efficacy Analysis**

Primary endpoint: According to the basic principle of intention-to-treat analysis, Chi-square test or Fisher's exact test will be used for data in the modified intention-to-treat cohort to evaluate efficacy. In addition, a logistic regression model will be adopted to calculate the odds ratio (OR) between the two treatment regimens, with center effects set as random effects in the model.

Secondary endpoint: The primary endpoint analysis strategy will be used for most secondary endpoint analyses. Wilcoxon rank-sum test will be used for measurement data to analyze differences between the two groups. For survival data, the Kaplan-Meier method will be used to estimate the survival rate of each group and plot survival curves, log-rank test will be used for efficacy evaluation, and Cox proportional hazards model will be used to calculate the hazard ratio (HR) between the two treatment regimens. For non-survival data, Chi-square test or Fisher's exact test will be used, and a logistic regression model will be used to calculate the OR value. Center effects will be set as random effects in all the models.

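### Continuous secondary outcomes are tested without conditioning on the Visit 1 value, and last observation carried forward is fixed with no exception for laboratory values or for death

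*Protocol*

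**What the plan says.** Protocol 13.2.2 assigns one test to all continuous secondary outcomes: "Wilcoxon rank-sum test will be used for measurement data to analyze differences between the two groups". The only adjustment named is for centre, and only in models: "Center effects will be set as random effects in all the models". A rank-sum test is not a model, so neither centre nor baseline enters it. The same section provides an odds ratio for binary data and a hazard ratio for survival data, but no effect estimate for measurement data.

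Section 4.2 defines the outcomes in two ways. Two are changes: "Change in NIHSS score at 3 months after randomization" and "Change in Barthel Index (BI) score at 3 months and 12 months". EQ-5D is worded otherwise, "Difference of EuroQoL Group 5-Dimension (EQ-5D) score at 3 months and 12 months after", and so are the platelet and coagulation outcomes. For these the reference is not stated: it could be the other group or the patient's own baseline.

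Section 13.1.1 sets the missing-data rule for the modified intention-to-treat cohort: "missing values will be estimated using the last observation carried forward method". It names no exception, and this cohort carries the efficacy conclusions: "The modified intention-to-treat population will be the primary population for efficacy evaluation in this study".

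Sections 6.1 and 6.1.1 collect NIHSS, BI, EQ-5D, platelets, PT and APTT at Visit 1 and designate those results as baseline. The visit schedule has laboratory tests at Day 1 and month 3 only. Appendix 2 gives the mRS a grade for death. Appendices 3 to 5 give none for NIHSS, EQ-5D or BI.

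**The concern.** There are three separate weaknesses.

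- **Precision.** A baseline is collected for every one of these outcomes, and the stated test either subtracts it or, on one reading of section 4.2, ignores it. Conditioning on it would be more efficient at no cost in data.
- **Laboratory values.** A patient with no month-3 sample receives the pre-treatment value, which cannot carry any treatment effect. These outcomes bear on bleeding, and the Background credits a component of the drug with inhibiting platelet aggregation, so dilution towards no difference is unwelcome.
- **Death.** If a score absent because of death counts as missing, LOCF supplies a living score. As an illustration, a patient with BI 60 at month 1 who dies at week 8 would be analysed as BI 60 at months 3 and 12. Missingness may also be informative short of death: section 6.2.1 allows withdrawal after an SAE or worsening symptoms, although 7.6.2 asks for follow-up to continue after the drug is stopped.

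**Working it through.** **The plan's own figure.** The protocol gives no sample size or power for the continuous outcomes. Its figure for the primary outcome (45% v 50.4%, two-sided 0.05, power 0.80) reproduces:

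n = [1.960·√(2·0.477·0.523) + 0.842·√(0.45·0.55 + 0.504·0.496)]² / 0.054² = 1342 per group, and 1342/0.90 rounds up to 1492.

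The point made here leaves that figure unchanged. 1342 is used below as the evaluable number per group.

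**Baseline adjustment.** Assume equal variance σ² at baseline and follow-up, and correlation r between them. The protocol gives no r, so 0.3 to 0.8 is an assumption.

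- Follow-up value alone: σ²
- Change: 2σ²(1−r)
- Follow-up value adjusted for baseline: σ²(1−r²)
- Adjusted relative to change: (1−r²)/[2(1−r)] = (1+r)/2
- Adjusted relative to follow-up alone: 1−r²

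The effect giving 80% power on follow-up values is (1.960+0.842)·√(2/1342) = 0.108 SD. At that effect:

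| r | Sample needed v change | Sample needed v follow-up alone | Power: follow-up / change / adjusted |
|---|---|---|---|
| 0.3 | 0.65 | 0.91 | 80 / 66 / 84% |
| 0.4 | 0.70 | 0.84 | 80 / 73 / 86% |
| 0.5 | 0.75 | 0.75 | 80 / 80 / 90% |
| 0.6 | 0.80 | 0.64 | 80 / 88 / 94% |
| 0.7 | 0.85 | 0.51 | 80 / 95 / 97% |
| 0.8 | 0.90 | 0.36 | 80 / 99 / 99.7% |

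Adjustment is better at every r in the range. The NIHSS and BI rows to read are those against change. For EQ-5D and laboratory values the comparison depends on what the difference is measured from.

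**Laboratory LOCF.** Let a share m of each arm lack a month-3 sample and receive the Day 1 value. Randomisation gives Day 1 values no expected group difference, so with equal m and missingness unrelated to outcome:

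expected difference = (1−m)·true difference + m·0

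If m equals the 10% loss assumed in section 13.3, the difference shrinks to 0.90 of its true size. This holds whether the outcome is change from baseline (carried value = zero change) or the month-3 value itself.

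**Death.** Rank-sum tests were simulated at 1342 per group, 500 runs per scenario, with no effect in survivors. Assumed inputs: change SD 2.7, mean change −3 in survivors, mean carried-forward change −1 in those who die, and mortality as shown. Lower is better, as on the NIHSS.

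| Mortality by arm | Rejection, LOCF | Rejection, worst rank for death |
|---|---|---|
| 1% / 1% | 5.6% | 4.6% |
| 2% / 1% | 6.0% | 8.4% |
| 3% / 1% | 5.6% | 14.6% |
| 5% / 2% | 9.8% | 26.6% |
| 6% / 2% | 10.4% | 44.6% |

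With few, balanced deaths the choice hardly matters. With unequal mortality, LOCF largely masks the difference on these scales.

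**The case against.** The strongest reply is that an unadjusted rank-sum test is valid in a randomised trial, that preferring adjustment is a matter of efficiency, and that covariates, effect estimates and death rules often sit in a separate analysis plan, to which section 13 refers. Validity is conceded, and the protocol does not forbid additional adjusted analyses. But the protocol itself states both the test and the imputation rule, so an analysis plan that replaced either would depart from it.

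Other objections stand and set the limits of the point:

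- A reader might infer that the measured baselines are thrown away. Section 4.2 does not support this for NIHSS and BI, which are changes. For EQ-5D and laboratory values the wording leaves it open.
- A reader might infer that early death could make the treatment look beneficial. Nothing shows this. In a recovering population a score carried from month 1 would usually be worse than survivors' later scores, as the simulation assumes. The result is masking, not reversal. The protocol also does not say outright that deaths count as missing.
- A reader might infer that a lethal effect would escape the trial. It would not: death is mRS 6 in the primary outcome, all-cause mortality is a safety outcome (4.4), vascular death is in the composite (4.2), and every death has a narrative (13.2.3).
- Not every patient without a month-3 sample is necessarily affected. The cohort requires an efficacy evaluation, 6.2.3 removes patients with no test records after dosing, and the discontinuation visit, whose content is not listed, might yield a sample.
- The variance formulas are for linear models. NIHSS and BI are bounded scales, and entry NIHSS is restricted to 4 to 15, so equal variances are doubtful.
- Worst-rank scoring changes the question. Its 44.6% rejection with no effect in survivors is a mortality signal, so it should not be the main analysis.

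**Conclusion.** The point holds for secondary outcomes only. The stated test gives up precision that a baseline already collected would supply. As a normal-theory approximation, adjustment needs 65% to 90% of the sample required with change scores, and 91% to 36% of that required with follow-up values alone, for assumed r of 0.3 to 0.8. LOCF of laboratory values dilutes group differences, to about 0.90 of their size if 10% of samples are missing equally and non-informatively. LOCF past death, if deaths are treated as missing, can mask a mortality difference on NIHSS, BI and EQ-5D. The size of that effect depends wholly on mortality, which the protocol does not give, and is negligible at 1% in both arms. The primary outcome and the stated sample size are unaffected.

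**What to change.** - **Section 4.2:** state what the EQ-5D and laboratory differences are measured from.
- **Section 13.2.2:** analyse the follow-up value with its Visit 1 value as covariate and centre as random effect. Name one method per outcome in advance, for example a proportional-odds model for NIHSS, BI and EQ-5D and linear ANCOVA for laboratory values. Report an effect with its 95% CI.
- **Section 13.1.1, laboratory values:** exempt them from LOCF, analyse observed month-3 values, and report the number missing by arm.
- **Section 13.1.1, death:** state that LOCF does not apply after death for NIHSS, BI and EQ-5D, say which patients the main analysis then covers, and add a worst-rank analysis as a sensitivity analysis.

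The cost is protocol wording and programming before unblinding, with no new visits, data or patients. Three drawbacks should be acknowledged: the proportional-odds assumption needs checking; observed-value laboratory analysis leaves out those who did not return, hence the count by arm; and scores restricted to patients alive must be read beside mortality.

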##### **13.2.3 Safety Analysis**

AEs and SAEs that have occurred will be listed separately and pooled for analysis. In each treatment group, the number and proportion of cases experiencing AEs will be pooled by system classification and items of interest. In addition, all deaths and SAEs will be described in detail in case narratives.

##### **13.2.4 Interim Analysis**

No interim analysis will be conducted in this study.

##### **13.2.5 End-of-Study Follow-Up**

Data collected from each group at the end of the study visit will be reported using descriptive statistics. The modified intention-to-treat cohort will be used for the analysis of efficacy outcomes, and the safety cohort will be used for the analysis of AEs.

### 13.3 Sample Size Determination

Based on previous findings, assuming that the proportion of patients in the control group with mRS  $\leq 2$  at 3 months is 45%, and the proportion in the XST group is relatively increased by 12%, with the significant level of 0.05 and the power of 0.80, 1342 patients are required in each group, and considering 10% lost to follow-up, 1492 patients are required in each group. Rounded to an integer, this trial is expected to enroll 3000 patients.

| Power  | Sample size
of the XST
group | Sample size
of the control
group | Response
rate of IMP | Response rate
of control
drug | Difference in
response rate
between the two
groups | Significant
level |
|--------|------------------------------------|----------------------------------------|-------------------------|-------------------------------------|-------------------------------------------------------------|----------------------|
| 0.8000 | 2389                               | 2389                                   | 0.4400                  | 0.4000                              | 1.100                                                       | 0.0500               |
| 0.8000 | 1931                               | 1931                                   | 0.4950                  | 0.4500                              | 1.100                                                       | 0.0500               |
| 0.8001 | 1565                               | 1565                                   | 0.5500                  | 0.5000                              | 1.100                                                       | 0.0500               |
| 0.8001 | 1977                               | 1977                                   | 0.4440                  | 0.4000                              | 1.110                                                       | 0.0500               |
| 0.8002 | 1597                               | 1597                                   | 0.4995                  | 0.4500                              | 1.110                                                       | 0.0500               |
| 0.8002 | 1293                               | 1293                                   | 0.5550                  | 0.5000                              | 1.110                                                       | 0.0500               |
| 0.8001 | 1663                               | 1663                                   | 0.4480                  | 0.4000                              | 1.120                                                       | 0.0500               |
| 0.8001 | 1342                               | 1342                                   | 0.5040                  | 0.4500                              | 1.120                                                       | 0.0500               |
| 0.8004 | 1086                               | 1086                                   | 0.5600                  | 0.5000                              | 1.120                                                       | 0.0500               |
| 0.8002 | 1419                               | 1419                                   | 0.4520                  | 0.4000                              | 1.130                                                       | 0.0500               |
| 0.8001 | 1144                               | 1144                                   | 0.5085                  | 0.4500                              | 1.130                                                       | 0.0500               |
| 0.8001 | 924                                | 924                                    | 0.5650                  | 0.5000                              | 1.130                                                       | 0.0500               |
| 0.8002 | 1225                               | 1225                                   | 0.4560                  | 0.4000                              | 1.140                                                       | 0.0500               |
| 0.8003 | 987                                | 987                                    | 0.5130                  | 0.4500                              | 1.140                                                       | 0.0500               |
| 0.8001 | 796                                | 796                                    | 0.5700                  | 0.5000                              | 1.140                                                       | 0.0500               |
| 0.8002 | 1068                               | 1068                                   | 0.4600                  | 0.4000                              | 1.150                                                       | 0.0500               |
| 0.8003 | 860                                | 860                                    | 0.5175                  | 0.4500                              | 1.150                                                       | 0.0500               |
| 0.8002 | 693                                | 693                                    | 0.5750                  | 0.5000                              | 1.150                                                       | 0.0500               |

[figure not shown]

794

#### 795 14. Principles for Protocol Amendment

796 All amendments to the protocol will be signed by all the signatories of the original protocol and recorded.

#### 797 15. Principles and Criteria for Complete Termination of the Trial

- 798 • Serious safety issues occur;
- 799 • The drug is found to have a poor response or is even ineffective without any value;
- 800 • Major errors are found in the study protocol or major deviations occur during the implementation of the
- 801 protocol, making it difficult to evaluate the drug effect;
- 802 • Discontinuation requested by the sponsor (due to cost or management issues);
- 803 • Authorization for the trial is revoked by the administrative authority.

#### 804 16. Confidentiality

805 Personal medical information of patients obtained during the trial will be considered confidential and will not

806 be disclosed to any third party except in the following circumstances:

- 807 1. Related medical information may be provided to the patient's physician in charge, or to other relevant
- 808 physicians;
- 809 2. Data related to this trial may be provided to the following personnel and agencies for review, including
- 810 participating physicians, sponsor's representative, ethics committees, and relevant regulatory authorities.

Further protection will be provided to patients via patient's identification code.

## **Appendix 1. Diagnostic Criteria for Ischemic Stroke (Excerpts)**

Diagnosis of ischemic stroke will be made according to the criteria set in the Fourth National Cerebrovascular Disease Conference of the Chinese Medical Association.

### **1. Atherosclerotic thrombotic cerebral infarction**

- 1) Usually occurring at rest;
- 2) Mostly without obvious headache or vomiting;
- 3) Slow onset, typically progressive or periodic, usually related to cerebral atherosclerosis, and also seen in arteritis and hematological diseases;
- 4) Clear consciousness or mild disorder of consciousness generally 1-2 days after the onset;
- 5) Symptoms and signs of internal carotid artery system and/or vertebrobasilar system;
- 6) CT or MRI examination is required;
- 7) Lumbar puncture cerebrospinal fluid will normally contain no blood.

### **2. Cerebral embolism**

- 1) Most cases have a sudden onset;
- 2) Most show no prodromal symptoms;
- 3) Clear consciousness or transient disorder of consciousness in general;
- 4) Symptoms and signs of internal carotid artery system and/or vertebrobasilar system;
- 5) Lumbar puncture cerebrospinal fluid will normally contain no blood, and hemorrhagic cerebral infarction may be considered if red blood cell is present;
- 6) Emboli can be classified into cardiogenic and non-cardiogenic emboli by source, and can be accompanied by embolism symptoms in other organs, skin, and mucous membranes.

### **3. Lacunar infarction**

- 1) The disease is mostly due to arteriosclerosis in hypertension patients, characterized by acute or subacute onset;
- 2) Most cases have no disorders of consciousness;
- 3) CT or MRI examination is required to for clear diagnosis;
- 4) Clinical manifestations are not serious, commonly including pure sensory stroke, pure motor hemiplegia, ataxic hemiparesis, dysarthria-clumsy hand syndrome, or sensorimotor stroke;
- 5) Lumbar puncture cerebrospinal fluid will contain no red blood cells.

### **4. Asymptomatic infarction**

This is a vascular disorder confirmed only by imaging for which no brain or retinal symptoms is documented, and the clinical diagnosis will be decided depending on the specific situation.

## Appendix 2. The modified Rankin Scale

The mRS will be used to assess patients' functional outcome after stroke. Only symptoms developing after the stroke will be considered. If a patient is able to walk with the support of some assistive devices and requires no external assistance, then the patient will be considered able to walk independently. If two grades seem equally applicable to the patient, and further questions are unlikely to help make an absolutely correct choice, the more serious grade will be chosen.

|                                                                                                                                                                                                                                                                                                                                                                                                                                                                                                                                                                                                               |
|---------------------------------------------------------------------------------------------------------------------------------------------------------------------------------------------------------------------------------------------------------------------------------------------------------------------------------------------------------------------------------------------------------------------------------------------------------------------------------------------------------------------------------------------------------------------------------------------------------------|
| 0-No symptoms at all                                                                                                                                                                                                                                                                                                                                                                                                                                                                                                                                                                                   |
| Despite possible mild symptoms, the patient does not experience any new functional limitations or symptoms since the occurrence of stroke.                                                                                                                                                                                                                                                                                                                                                                                                                                                                    |
| 1-No significant disability despite symptoms; able to carry out all usual duties and activities                                                                                                                                                                                                                                                                                                                                                                                                                                                                                                        |
| The patient experiences certain symptoms caused by stroke, no matter physically or cognitively (for example those affecting speaking, reading, or writing; physical movement; feeling; visual sense; swallowing; or emotion), but the patient is still able to engage in all the work and social and leisure activities that he/she could carry out prior to stroke. The key question used to distinguish grade 1 from grade 2 can be "Are there any things you did frequently in the past but can't do anymore after stroke?". Activities with a frequency more than once a month are considered "frequent". |
| 2-Slight disability; unable to perform all previous activities but able to look after own affairs without assistance                                                                                                                                                                                                                                                                                                                                                                                                                                                                                   |
| After stroke, the patient is unable to perform some previous activities that he/she could complete before stroke (e.g., driving, dancing, reading, or working), but the patient is still able to look after him/herself without assistance. The patient can dress, walk, eat, go to the bathroom, prepare simple food, go shopping, and travel locally without the help from others. And the patient can live without supervision. It is assumed that patients at this grade can live alone at home for one week or above in the absence of caregiver.                                                        |
| 3-Moderate disability; requiring some help but able to walk without assistance                                                                                                                                                                                                                                                                                                                                                                                                                                                                                                                         |
| Patients at this grade can independently walk (with or without the help of a walking aid), dress, go to the bathroom, and eat, but an assistance is required for more complex tasks. For example, shopping, cooking, or cleaning needs to be done by someone else, and visiting the patient more than once a week is necessary to ensure that these activities can be completed. Assistance is needed not just for physical care, but more for advice: for example, patients at this grade will need supervision or encouragement to deal with their finances.                                                |
| 4-Moderately severe disability; unable to walk without assistance and unable to attend to own bodily needs without assistance                                                                                                                                                                                                                                                                                                                                                                                                                                                                          |
| The patient needs others' help with daily life, regardless of walking, dressing, going to the bathroom, or eating. The patient needs care for at least once a day, usually twice or more, or must live within close proximity of a caregiver. To distinguish grade 4 from grade 5, consider whether the patient is able to live alone normally during appropriate time spans within a day.                                                                                                                                                                                                                    |
| 5-Severe disability; bedridden, incontinent, and requiring constant nursing care and attention                                                                                                                                                                                                                                                                                                                                                                                                                                                                                                         |
| The patient needs to be taken care several times throughout the day and night, although no trained nurses are required.                                                                                                                                                                                                                                                                                                                                                                                                                                                                                       |

921

